### 3.2 Primary Endpoint

- Cumulative postoperative opioid use measured as Milligram Morphine Equivalent (MME) up to 72 hours following catheter insertion, calculated based on the following conversion table [38]

| Opioids                         | Conversion Factor |
|----------------------------------------|--------------------------|
| Oral Opioids                    |                          |
| Codeine (mg)                           | 0.15                     |
| Tramadol (mg)                          | 0.1                      |
| Hydrocodone (mg)                       | 1                        |
| Oxycodone (mg)                         | 1.5                      |
| Methadone (mg/day)                     |                          |
| 1-20                                   | 4                        |
| 21-40                                  | 8                        |
| 41-60                                  | 10                       |
| ≥61-80                                 | 12                       |
| Morphine (mg)                          | 1                        |
| Hydromorphone (mg)                     | 4                        |
| Transdermal Opioids             |                          |
| Fentanyl ( $\mu\text{g}/\text{hour}$ ) | 2.4                      |
| Intravenous Opioids             |                          |
| Morphine (mg)                          | 3                        |
| Hydromorphone (mg)                     | 15                       |
| Fentanyl ( $\mu\text{g}$ )             | 0.2                      |

### 3.3 Secondary Endpoints

- Median pain score as measured by a standardized numeric rating scale over 72 hours following catheter insertion (measured at rest and with coughing q12hours  $\pm$  2 hours post-catheter insertion)
- Cumulative postoperative opioid use measured as Milligram Morphine Equivalent (MME) from catheter insertion until discharge from hospital

- Assessment for delirium BID for 72 hours following catheter insertion, as defined by the presence of one of the following criteria: Confusion Assessment Method (CAM) or CAM-ICU positive, or Intensive Care Delirium Screening Checklist (ICDSC) >3, or 3D-CAM, or 4AT  $\geq 4$ , or more than one dose of haloperidol or similar antipsychotic drug, or documented delirium by neurologist or psychiatrist consultation
- Quality of Recovery-15 Scale administered 24-96 hours post-surgery

### 3.4 Tertiary (exploratory) Endpoints

- Time from catheter insertion to extubation
- Time from catheter insertion to first opioid analgesic provision following extubation
- Time from catheter insertion to mobilization
- ICU and hospital LOS
- Postoperative nausea and vomiting, measured via a 10-point visual analogue scale BID and antiemetic medication requirements up to 72 hours following catheter insertion
- Opioid requirements post-discharge as assessed by prescriptions provided at time of discharge and during post-discharge follow-up visit using both patient health record and direct patient recounting
- Chronic post sternotomy pain/disability and patient reported outcomes assessed at 3 months  $\pm$  4 weeks from surgery with McGill Pain Questionnaire as well as at 6 weeks  $\pm$  2 weeks and 3 months  $\pm$  4 weeks with the change in PROMIS 29 score (Attempts to obtain the 3-month data can continue for up to 6 months post-surgery before it will be considered a protocol deviation or the participant deemed lost-to-follow-up)

### 3.5 Randomization Procedure

Randomization will be performed via a centralized, web-based platform that uses permuted blocks of varying sizes. Randomization will be stratified by site and patient sex. Dedicated unblinded individuals at each site who are responsible for preparing the assigned blinded bags of ropivacaine and saline will be provided with a randomization code list. Details on participant allocation and the randomization code lists will not be shared with the blinded study team members.

### 3.6 Study Interventions

All patients will have their cardiac surgery and anesthesia as per standard of care. Patients assigned to either group will undergo administration of general anesthesia, endotracheal intubation, vascular access procedures, and transesophageal echocardiography probe insertion as per usual cardiac anesthesia practice. Usual anesthetic monitoring practice will continue before, during, and after the block is performed.

#### *Catheter Insertion*

Catheter insertion will be performed by an anesthesiologist with specialized regional block training. Catheters (Arrow® or PAJUNK®) will be inserted under ultrasound guidance, in a sterile fashion, with a high-frequency linear transducer which will be placed 1 cm lateral to the sternal border in the longitudinal plane in order to view the T4-T5 intercostal space. A 16 or 17-gauge Tuohy needle (or alternate catheter suitable nerve block needle) will be used to enter the superficial PIP, with saline being injected to help visualize the plane between the pectoralis major and intercostal muscles. Subsequently, the catheters will be advanced into the plane and secured on the skin.

#### *Study Intervention Administration:*

Bags of 0.2% ropivacaine and 0.9% saline will only be identifiable by the participants' unique study numbers on the labels and transported to the OR or ICU in UV light-resistant bags. The bags of ropivacaine and saline, still in their UV light-resistant bags will be set up in nerve block infusion pumps (e.g. CADD Solis [ICUMedical, San Clemente, California]) for administration. Following catheter insertion, the bags of ropivacaine and saline will be attached via dedicated tubing to each study drug administration catheter (one pump per catheter). An initial bolus of 20 mL per side of study intervention will be administered through the pumps. Subsequently, a basal infusion rate (0.1-1 mL/hr per side) will be initiated and will continue for 48 hours, with an additional 5 mL bolus every 3-4 hours for 48 hours. This will result in a total of 85-148 mL of study intervention per side (170-296 mL total) being administered to each patient during the study. This equates to a maximum of 592 mg of ropivacaine administered during the 48-hour drug administration period. This is well within accepted safe limits as described in the product monograph [39].

### 3.7 Blinding

The participants, clinical team, intervention applicers (i.e. the operating room staff), outcome assessors, and data entry support team will be blinded to the randomized treatment arm until the database is locked. Blinded study bags will be inserted into the infusion pumps. Unblinding procedures are available if necessary for clinical treatment e.g. cases of suspected local anesthetic systemic toxicity (LAST) or allergic reactions. Site investigators should contact the PI of the lead site ([name]) to request the code break. The date and reason(s) for breaking the blind must be recorded in the source documentation and electronic case report forms (eCRFs), as applicable.

## **4. Eligibility Criteria**

### 4.1 Inclusion Criteria

1. Adult patients undergoing cardiac surgery via median sternotomy

### 4.2 Exclusion Criteria

1. Redo sternotomy, or cardiac surgery performed through non-sternotomy approaches (minimally invasive procedures, thoracotomies, mini-sternotomy, hemi-sternotomy, etc.)
2. Emergency procedures (surgery within 2 hours)
3. Clinical instability which in the judgement of the investigator precludes enrollment or participation in the study.
4. Weight < 50 kg
5. Active systemic bacterial infection including infective endocarditis or pre-existing sternal infections
6. Surgery for infective endocarditis
7. Pregnancy or nursing
8. Chronic opioid/narcotic use > 6 weeks, active use of illicit drugs, long-term opioid exposure or opioid use and/or chronic pain disorder/syndromes
9. Allergies to amide anesthetic agents or any components of study interventions
10. Inability to comply with, or participate in, protocol (i.e. cognitive impairment/altered mental status/neurological deficit or disorder, inability to provide informed consent, inability to complete pain rating scales, etc.)
11. Receipt of an investigational drug or device within past 7 days

## 5. Study Procedure and Visits

### 5.1 Summary of Visits

Patients will be screened at an initial preoperative visit at which point eligibility will be determined. Patient outcomes will be assessed throughout their postoperative hospital stay as detailed above. Two follow-up telephone visits after the operation will be scheduled. The first will be at 6 weeks  $\pm$  2 weeks post surgery and the second will be at 3 months  $\pm$  4 weeks.

### 5.2 Study Visits

#### *Visit S: Screening*

- Written informed consent
- Determination of eligibility
- Demographics, medical history, baseline medications including doses
- Physical examination, height and weight assessment, BMI
- Vital signs
- Laboratory assessments: CBC, creatinine/eGFR, electrolytes, coagulation testing
- Preoperative PROMIS 29 Score

#### *Visit R: Preoperative Randomization*

- Confirmation of eligibility
- Randomization

#### *Hospitalization*

- Cumulative postoperative opioid use measured as Milligram Morphine Equivalent (MME) from catheter insertion until discharge from hospital, obtained via medication administration record (MAR) in patients' health record.
- Median pain score as measured by a standardized numeric rating scale over 72 hours following catheter insertion (measured at rest and with coughing q12hours  $\pm$  2 hours post-catheter insertion). First assessment will be conducted when patient is awake and able to follow commands following extubation, second assessment will be conducted at the first intervention dose following first assessment, and ongoing assessments will be conducted at approximately every 12 hours thereafter.

- Delirium assessed BID for 72 hours following catheter insertion (see above criteria). First assessment will be conducted when patient is awake and able to follow commands following extubation, second assessment will be conducted at the first intervention dose following first assessment, and ongoing assessments will be conducted at approximately every 12 hours thereafter.
- Time from catheter insertion to extubation
- Time from catheter insertion to first opioid analgesic provision following extubation
- Time from catheter insertion to mobilization
- ICU and hospital LOS
- Postoperative nausea and vomiting, measured via a 10-point visual analogue scale BID and antiemetic medication requirements up to 72 hours following catheter insertion. First assessment will be conducted when patient is awake and able to follow commands following extubation, second assessment will be conducted at the first intervention dose following first assessment, and ongoing assessments will be conducted at approximately every 12 hours thereafter.
- Quality of Recovery-15 Scale administered 24-96 hours post-surgery

*Visit P1: Postoperative Follow-Up: 6 weeks  $\pm$  2 weeks post surgery (Phone-Call Visits)*

- PROMIS 29 score
- Opioid requirements post-discharge as assessed by prescriptions provided at time of discharge and during post-discharge follow-up visit using both patient health record and direct patient recounting

*Visit P2: Postoperative Follow-Up: 3 months  $\pm$  4 weeks post surgery (Phone-Call Visit)*

- PROMIS 29 score
- McGill Pain Questionnaire
- Opioid requirements post-discharge as assessed by prescriptions provided at time of discharge and during post-discharge follow-up visit using both patient health record and direct patient recounting
- Attempts to obtain the 3-month data can continue for up to 6 months post-surgery before it will be considered a protocol deviation or the participant deemed lost-to-follow-up

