### 3.4.2 Secondary Efficacy Endpoints

Pain score during the 72 hours following catheter insertion will be analyzed by a mixed model for repeated measures (MMRM), with random effects for intercept and time, fixed effects for treatment, sex, and intraoperative MMEs (<median, ≥median), and an unstructured covariance matrix.

The analysis of cumulative postoperative opioid use measured as MMEs from catheter insertion until discharge from hospital will be by the same methods as for the primary efficacy endpoint, including the joint model sensitivity analysis.

The analysis of incidence of delirium during the 72 hours following catheter insertion will be by logistic regression with fixed effects for treatment group, sex, and intraoperative MME (<median, ≥median). The treatment odds ratio (OR) and associated 95% confidence interval will be provided.

The analysis of Quality of Recovery-15 Scale administered 24-96 hours post-surgery will be by the same methods as for the primary efficacy endpoint.

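### Pain scores follow two timing rules that agree only by coincidence, and the SAP pain model lists no fixed effect of time to absorb the difference

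*Combined protocol and SAP*

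**What the plan says.** Protocol 3.3 defines the first-listed secondary endpoint as "Median pain score as measured by a standardized numeric rating scale over 72 hours following catheter insertion". Protocol 5.2 (Hospitalization) repeats it and gives the schedule: "measured at rest and with coughing q12hours", with a tolerance of ± "2 hours post-catheter insertion".

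The same bullet then gives a second schedule:

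- the opening score is taken once the extubated patient has woken and responds to instructions;
- for the next score, the rule is: "second assessment will be conducted at the first intervention dose following first assessment";
- for all scores after that, the rule is: "ongoing assessments will be conducted at approximately every 12 hours thereafter".

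The delirium and nausea bullets carry this second schedule too, but their stated frequency is only twice daily, with no ± 2 h window.

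Protocol 3.6 sets the doses: an initial bolus, a continuous basal infusion, and then "with an additional 5 mL bolus every 3-4 hours for 48 hours". Because the basal infusion never pauses, an intervention dose in the assessment rule has to mean a bolus.

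SAP 3.4.2 analyses pain with a repeated-measures mixed model, not a per-patient median. It has random effects for intercept and time, fixed effects for treatment, sex and intraoperative MMEs, "and an unstructured covariance matrix". Delirium is analysed as any occurrence, by logistic regression. The analysis windows in SAP 3.1.2 cover Days 0, 42 and 91 only.

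**The concern.** An assessor cannot in general follow both pain schedules. One is tied to insertion, the other to extubation and then to a pump bolus. Time from insertion to extubation is itself a trial endpoint (Protocol 3.4), and the protocol's introduction cites a randomised trial of a continuous block of this kind that found it shortened. If the block changes extubation time here, the two arms will be scored at different times since surgery.

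Pain after sternotomy is unlikely to be constant over 72 h, so a shift in scoring times can look like a treatment effect or hide one. The protocol's median has a further problem: two scores taken close together around extubation count as much as two scores taken 12 h apart.

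**Working it through.** **Dose interval.** The assessment rule depends on the bolus spacing, so I first reproduced the stated volume per side: 20 + 5 × (48 / interval) + rate × 48.

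- 4 h interval, 0.1 mL/h: 20 + 60 + 4.8 = 84.8 mL.
- 3 h interval, 1 mL/h: 20 + 80 + 48 = 148 mL.

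This matches the stated 85-148 mL and confirms 12 to 16 boluses spaced 3-4 h apart.

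**Second schedule.** Let E be hours from insertion to the first awake assessment, taken as the extubation time, with boluses on a regular grid from insertion. Then t1 = E, t2 = first bolus after E, and later scores fall at t2 + 12, t2 + 24, ... up to 72 h. A score is in window if it lies within 2 h of 12, 24, 36, 48, 60 or 72 h. Because the later scores are 12 h apart, a patient's scores from the second on are either all in window or all out.

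| E | Bolus interval | Scores (h) | In window |
|---|---|---|---|
| 5 h | 3 h | 5, 6, 18, 30, 42, 54, 66 | 0 of 7 |
| 7 h | 4 h | 7, 8, 20, 32, 44, 56, 68 | 0 of 7 |
| 9 h | 4 h | 9, 12, 24, 36, 48, 60, 72 | 6 of 7 |
| 10 h | 3 h | 10, 12, 24, 36, 48, 60, 72 | 7 of 7 |

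Rows two and three show the sensitivity: extubation 2 h earlier moves every score from the second on by 4 h.

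**How many scores miss the window.** The documents give no extubation time, so E is assumed. Share of all scores outside the window, with E uniform over the range shown:

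| Range of E | 3 h boluses | 3.5 h | 4 h |
|---|---|---|---|
| 0-24 h | 75% | 63% | 68% |
| 4-8 h | 100% | 79% | 100% |
| 6-12 h | 52% | 25% | 38% |

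With lognormal E (median 4-12 h, sigma 0.5), the share of patients in window from the second score on is 4-28% (3 h), 12-55% (3.5 h) and 7-38% (4 h). Allowing sigma from 0.3 to 0.5, and also a gap to the second score drawn evenly from 0-4 h, the full range is about 0% to 76%. The top, 73-76%, occurs at a median of 9-10 h, sigma 0.3 and 3.5 h boluses.

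**Spacing reading.** If ± 2 h is instead a tolerance on the interval (10-14 h between scores), E = 4 h with 3 h boluses gives gaps of 2, 12, 12, 12, 12 and 12 h. Only 1 gap of 6 fails.

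**Early pair.** For E below 12 h there are usually 7 scores. The first two make up 2/7 = 29% of them, yet span at most 4 h, or 4/72 = 5.6% of the period. With E uniform over 0-24 h, their mean gap is 1.5 h (3 h boluses) to 2.0 h (4 h boluses).

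**Undefined case.** For E = 50 h no bolus follows, so neither the second assessment nor anything counted from it has a time.

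**Route into the analysis.** SAP 3.4.2 names time only as a random effect, so no mean time trend is listed. If mean scoring times differ between arms by d hours and pain changes by b points per hour, a difference of up to about b × d can be taken up by the treatment term. The documents give neither b nor d.

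**The case against.** A reader might infer that most scores fall outside the window. The documents do not establish that. It needs both the insertion-anchored reading and an assumed extubation time. With extubation at about 9-12 h nearly all scores are in window, and under the spacing reading only the first gap fails.

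A reader might extend the window argument to delirium and nausea. It does not reach them: they are twice daily with no tolerance. They share only the early pair and the undefined second assessment, and any-occurrence delirium has no weighting to distort, although an extra early look adds one chance of detection.

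A reader might say the early pair gets double weight in the planned analysis. That is true of an unweighted median. In a mixed model, the influence of two close, correlated scores depends on the covariance, so 29% is a share of scores and not of influence.

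A reader might say an unstructured covariance requires common time points. That holds for residuals over categorical visits. The phrase may equally describe the random intercept and slope, which accept irregular times. The SAP wording does not settle which.

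It is also fair that self-reported pain cannot be scored before a patient wakes, that the primary opioid endpoint is untouched, and that no bias has been quantified. If the block does not alter extubation, scoring times vary but should balance between arms. What still stands is the contradiction within one bullet, the dependence of scoring times on a post-randomisation event, and the lack of anything in the SAP that handles it.

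**Conclusion.** The point holds for pain in a limited form. Protocol 5.2 gives two schedules that coincide only when the bolus after extubation falls near a multiple of 12 h. Many scores can miss the insertion-based window, but the number cannot be fixed from the documents: the in-window share from the second score on runs from about 0% to 76%, depending on assumed extubation times and bolus interval. The early pair, at most 3-4 h apart, supplies about 2 of 7 scores in the protocol's median. The second assessment is undefined after the last bolus, for pain, delirium and nausea alike.

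The main statistical consequence is that the SAP pain model, as listed, does not separate time since insertion from treatment. Bias is possible rather than shown: it requires scoring times that differ between arms and pain that changes over those hours. This should be corrected, but it does not threaten the primary analysis.

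**What to change.** **Protocol 3.3 and 5.2.** State one anchor for the research assessments. Catheter insertion is the natural choice because the endpoint already names it. Remove the link to the next intervention dose, and keep the first-awake score as a separately labelled additional assessment. The dose-linked clause also appears under delirium and nausea and needs the same reconciliation there. No dose or clinical rule is affected.

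**SAP 3.4.2.** Add time since catheter insertion as a fixed effect, with treatment-by-time. Use either the actual recorded times or stated nominal windows with a rule that keeps off-window scores instead of discarding them. Say whether unstructured refers to the random effects or the residuals.

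**Cost.** A protocol clarification and a few lines of SAP text. For patients already enrolled, only the SAP change applies. The limitation is that slots before extubation will be missing, and that missingness still depends on extubation time. Report the number of such slots by arm.

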## **6. Subject Safety Monitoring and Adverse Events**

Risks associated with the proposed intervention include: infection (both soft tissue and intravascular), hematoma/bleeding, vascular injury, pneumothorax/hemothorax and allergic reaction/anaphylaxis [24]. In an investigation of intermittent bolus erector spinae plane blocks in cardiac surgical patients receiving lateral mini-thoracotomy, adverse events included: pneumothorax (~1%), stasis around stoma (~5%, generally less than 10 mL), hypotension (~1%), catheter displacement (~3%), and catheter obstruction secondary to clotting (~2%) [40]. The most common adverse effects to ropivacaine specifically are: hypotension (32%), nausea (17%), vomiting (7%), bradycardia (6%), and headache (7%) [41]. Furthermore, local anesthetic systemic toxicity (LAST) occurs at a rate of approximately 1.8 in 1000 local anesthetic administrations [42]. Signs and symptoms generally manifest within 1-5 minutes of administration and include oral numbness, metallic taste, dizziness, drowsiness and disorientation; more severe manifestations can appear up to 6 hours after initial symptoms and may include seizures, arrhythmias, hypotension, cardiac arrest and death. Continuous blockade via catheter delivery of local anesthetic may increase risk of LAST compared with single-shot techniques, although ropivacaine is associated with less cardiotoxicity than other local anesthetics [43, 44]. In addition, patients with cardiac disease are at an increased risk of LAST. In particular, those with conduction disorders may have a higher risk of cardiotoxicity. As such, the use of less cardiotoxic drugs like ropivacaine is recommended for these patients [44]. Ropivacaine also has a higher cardiovascular collapse/CNS ratio compared with racemic bupivacaine, and therefore has a theoretical safety advantage for long-acting local anesthetic purposes [44]. Nevertheless, current evidence suggests PIF blocks are safe and easy to perform, especially considering the more superficial location of the plane (and therefore the increased distance from vital structures) compared with a deep PIP or transversus thoracis muscle plane block [24].

In the present investigation, each study visit will include safety monitoring. Adverse effects that will be specifically collected include infection, hematoma/hemorrhage, vascular injury, pneumothorax/hemothorax, allergic reaction/anaphylaxis, postoperative nausea/vomiting, pruritus and LAST. Adverse event data will be reported in the study publication.

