#### 3.5.1 *Adverse Events (AEs)*

AEs will be categorized according to the types specified in the CRF and summarized by treatment group.

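### Protocol section 6 gives rates for hypotension, bradycardia, headache and catheter failure, but neither its collection list nor the SAP ensures that they are counted by arm

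*Combined protocol and SAP*

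**What the plan says.** The first paragraph of protocol section 6 reviews the expected harms and attaches rates to several. For the drug: "The most common adverse effects to ropivacaine specifically are: hypotension (32%), nausea (17%), vomiting (7%), bradycardia (6%), and headache (7%) [41". For catheters, it draws on a cohort with intermittent-bolus erector spinae plane blocks after cardiac surgery: "hypotension (~1%), catheter displacement (~3%), and catheter obstruction secondary to clotting (~2%) [40". That cohort also supplies pneumothorax (about 1%) and stasis around the stoma (about 5%). For systemic toxicity (LAST): "local anesthetic systemic toxicity (LAST) occurs at a rate of approximately 1.8 in 1000 local anesthetic administrations [42". Its severe forms "may include seizures, arrhythmias, hypotension, cardiac arrest and death".

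The second paragraph says what will be recorded: "Adverse effects that will be specifically collected include infection, hematoma/hemorrhage, vascular injury, pneumothorax/hemothorax, allergic reaction/anaphylaxis, postoperative nausea/vomiting, pruritus and LAST". It adds that every study visit includes safety monitoring and that adverse event data will be published.

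In the SAP, section 2.3.4 names two safety endpoints, postoperative laboratory tests and transfusions. Section 3.5.1 adds: "AEs will be categorized according to the types specified in the CRF and summarized by treatment group". The case report form is not among the documents. Section 3.5 limits safety analysis to description. Protocol section 6.1 has the data and safety monitoring board (DSMB) review safety reports once half the trial population has completed follow-up, and allows it to ask for more.

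**The concern.** The two paragraphs of section 6 do not match. Of the five ropivacaine effects given a rate, only nausea and vomiting reach the collection list; the one rated most common, hypotension, does not. Pruritus, which has no rate in the text, is listed. Neither type of catheter failure is listed.

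Two things are at stake. The first is the safety conclusion. The trial means to establish the block definitively, and whether ropivacaine adds hypotension or bradycardia over saline is an obvious question for it. If these events are not actively sought, an analyst cannot recover them later, and a short adverse event table may mean only that nobody asked.

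The second is the reading of a null primary result. A displaced catheter, or one blocked on one side of a bilateral block, may deliver little drug while the pump runs on. Without a record of such failures it is hard to tell an ineffective block from an undelivered one. Protocol section 7 also promises a per-protocol sensitivity analysis, and deciding who received the block as planned calls for the same information.

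**Working it through.** **Set side by side (protocol section 6)**

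| Event | Rate given | On the collection list? |
|---|---|---|
| Hypotension | 32% (drug); ~1% (catheter cohort) | No |
| Nausea; vomiting | 17%; 7% | Yes |
| Headache | 7% | No |
| Bradycardia | 6% | No |
| Stasis around stoma | ~5% | No |
| Catheter displacement | ~3% | No |
| Catheter obstruction | ~2% | No |
| Pneumothorax | ~1% | Yes |
| LAST | 1.8 per 1000 | Yes |
| Pruritus | none | Yes |

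Nothing elsewhere in the protocol or SAP names hypotension, bradycardia, headache or catheter failure as a collected outcome. Hypotension and arrhythmia appear only as possible signs of severe LAST.

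**Arm size.** SAP section 2.2.2 gives a difference of 10 MME, SD 25, two-sided 5% and 90% power. The normal approximation is n = 2(1.96 + 1.2816)² × 25²/10² = 131.3, so 132 per group. The exact t calculation gives 133, with power 0.9015. The plan's 133 reproduces. With 340 randomised 1:1, the upper figure is 340/2 = 170 per arm. The point does not depend on this calculation; it only supplies arm sizes.

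**Expected ropivacaine-arm counts (n × rate), if the cited rates applied**

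| Event | n = 133 | n = 170 |
|---|---|---|
| Hypotension at 32% | 42.6 | 54.4 |
| Hypotension at 1% | 1.3 | 1.7 |
| Headache at 7% | 9.3 | 11.9 |
| Bradycardia at 6% | 8.0 | 10.2 |
| LAST at 0.18% | 0.2 | 0.3 |

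The LAST row treats each patient as one administration.

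**Catheter events, both arms, since all patients have catheters**

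- Displacement: 266 × 0.03 = 8.0; 340 × 0.03 = 10.2.
- Obstruction: 266 × 0.02 = 5.3; 340 × 0.02 = 6.8.
- Sum, assuming no patient has both: 13.3 to 17.0.

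**What by-arm counts could show.** Assuming the same rate p in both arms, the 95% half-width for the difference is 1.96 × √(2p(1 − p)/n):

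- p = 0.32: 11.2 points (n = 133) to 9.9 (n = 170).
- p = 0.06: 5.7 to 5.0 points.

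The documents give no saline-arm rate, so equal rates are my assumption. These figures describe how informative a descriptive summary would be. The SAP plans no safety test.

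**The case against.** The strongest reply is that nothing here shows the events will go unrecorded. The list is introduced as a set of inclusions, not a closed set. Every visit has safety monitoring, and the case report form, which fixes the types for the SAP table, cannot be inspected. This stands. A reader might infer that the trial cannot report these harms; the documents support only that their collection and reporting are not prespecified.

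A reader might also infer that the DSMB sees only this list. No passage says so, and section 6.1 lets the board request further analyses. It can, however, analyse only what was recorded.

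Nor should 32% be taken as the rate to expect. The catheter cohort, which is closer in technique and setting, gives about 1%. The spread is itself a reason to count, but any magnitude needs both ends.

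Catheter failure is partly covered. SAP section 3.3.1 tabulates treatment discontinuation with its primary reason, section 3.4.1 treats discontinuation and rescue block as intercurrent events, and a sensitivity analysis models rescue block. A failure that ended the infusion should surface there. What may be missed is failure without discontinuation.

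Finally, LAST is listed, usual anaesthetic monitoring continues during and after the block (protocol section 3.6), and the blind can be broken if LAST is suspected. So signs in an anaesthetised patient need not go unobserved. But LAST does not stand in for the omitted events. Its early symptoms are largely self-reported, and the 20 mL per side bolus follows catheter insertion, when patients are still to be extubated. A fall in blood pressure not attributed to LAST has no named place on the list.

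**Conclusion.** The mismatch within section 6 is real, and the SAP does not close it. As written, the documents do not ensure by-arm counts of hypotension, bradycardia or headache, or of catheter failures that leave treatment running. This limits the safety conclusion and the interpretation of a null result. It does not touch the primary analysis, the sample size or the error rate, and no planned test is lost.

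The size is uncertain because the cited rates are. At 133 to 170 ropivacaine patients, hypotension could number 1 to 2 or 43 to 54, and bradycardia about 8 to 10. About 13 to 17 catheter events are expected over 266 to 340 patients. All this assumes that rates from other settings carry over to this block and, for the catheter total, that the two events do not overlap. By contrast, the listed LAST item is likely to be empty or nearly so. If the case report form already has these fields, what remains is to say so in the protocol and SAP.

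**What to change.** Add to the collection list in protocol section 6: hypotension and bradycardia, each with a recording definition fixed in advance (for example, events that were treated); headache; and catheter displacement or obstruction, with side and time. Decide openly whether stasis around the stoma belongs there too. Put the same items on the case report form unless they are already captured, in which case state that.

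Name them in SAP section 3.5.1 for descriptive summary by arm in the Safety Population, and include them in the reports to the DSMB. This is recording only and alters no treatment or monitoring.

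The cost is a few extra fields. Background hypotension after cardiac surgery is likely to be common, so counts may be high in both arms; the blinded saline arm provides the comparison, and a tight definition keeps it readable. Protocol section 3.1 shows all four sites already recruiting, so patients already enrolled may need retrospective chart entry. That could be uneven, and the report should say which records were completed that way.
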